**Fig. 2 Fig2:**
[figure not shown]
Standard Protocol Items: Recommendations for Interventional Trails (SPIRIT) table of enrolment, intervention, and assessments

#### Standardized questionnaires

Participants complete quantitative, self-reported questionnaires including generic data in order to determine the primary and secondary outcome measurements.

#### Statutory health insurance data

Statutory health insurance (SHI) data will be analyzed for all study participants who provided consent and are insured by one of the participating insurance providers. The data include master data, diagnostic data, and treatment data (type of treatment, with the date and costs) of outpatient care by physicians, in-patient care in hospitals, drugs and medication, rehabilitation, reintegration, domestic help, inability to work, domestic nursing care, and nursing services. SHI data covers the time period 12 months before intervention to the complete intervention time. Survey data will be linked with SHI data at the individual level for each respondent who has given consent for data linkage.

#### Semi-structured interviews

Qualitative cross-sectional and sequential interviews with the healthy parent will be carried out in the IG and CG. The semi-structured interview takes approximately 30 min, with a narrative character. Open questions will give the interviewee sufficient scope for the answers. The content will focus on the current family situation, the way the family copes with it, the unmet support needs and available support, and communication aspects within the family. A particular focus in the intervention families will aim at the perceived support provided by the family-SCOUTs. The interviews will be audiotaped, transcribed according to Fuß and Karbach [17], and pseudonymized. The transcripts will be analyzed using Mayring’s qualitative content analysis [18].

## Sample size

On the basis of the project’s pilot phase, it is assumed that 265 families can be included in region 1 (Aachen) in the intervention group (IG). In region 2 (Bonn), it is assumed that a total of 135 families can be included, with 70 families in the control group (CG) in the first year, followed by 65 families in the IG. In region 3 (Düsseldorf), an estimated total of 160 families can be included in the CG. This results in the following sample sizes: IG = 265 + 65 = 330; CG = 70 + 160 = 230. In total *N*=560 families should be included.

A HADS responder rate of around 30% between T0 and T2 is expected in the IG. With the planned sample size, a difference of 28% (IG) versus 16% (CG) will then be identifiable at the 5% significance level with a power of 90% in the full analysis population (after imputation for missing values for dropouts, 330 in the IG, 230 in the CG) using Fisher’s exact test. After exclusion of dropouts of 20% per group between T0 and T1 and again 20% between T1 and T2, sample sizes of 211 (IG) and 147 (CG) remain, such that a complete case analysis could detect a difference from 30 to 16% still with a power of 85%. For the semi-structured interviews, approximately 30–40 healthy partners will be recruited in regions 1–4.

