The subpopulation with statutory health insurance (SHI) data will be investigated separately. The distribution of baseline variables will be compared between the subpopulations with and without SHI data. The target variables based on the SHI data will be analyzed descriptively and compared between IG and CG on individual level clusters adjusting for families. Costs and uptake will be analyzed in the health economic evaluation. Missing values for the clinical outcomes may arise due to dropouts (not filling the questionnaires at T0–T2, approx. 20% per group) or incomplete details.

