### Trial status

Recruitment of participants for the study commenced in October 2018, and the first family was included on October 9, 2018. On September 29, 2020, 406 families have been assigned, 216 into IG and 190 to CG; currently, 45 families have participated in the semi-structured interviews. The estimated enrollment period, including recruitment and inclusion, is anticipated to be 27 months (December 31, 2020) and will conclude, when the estimated sample size has been included. The version number and date of the protocol are v1.0 and July 6, 2018, respectively.

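### The stated 90% power for 28% versus 16% counts all 560 families as observed after imputation; with the plan's own 36% loss it is roughly 75–85%

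*Protocol article*

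**What the plan says.** Under Sample size, the protocol article adds up what each region is thought able to recruit: "IG = 265 + 65 = 330; CG = 70 + 160 = 230". It then states that "a difference of 28% (IG) versus 16% (CG) will then be identifiable", at the 5% level and with 90% power by Fisher's exact test, "in the full analysis population (after imputation for missing values for dropouts, 330 in the IG, 230 in the CG").

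The following sentence assumes "dropouts of 20% per group between T0 and T1 and again 20% between T1 and T2". It arrives at 211 and 147 remaining families and gives 85% power for a complete-case analysis of 30% versus 16%. The section names a responder rate of around 30% as the one expected in the intervention group.

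Statistical methods makes the family-level comparison of HADS response at nine months the primary analysis. It is carried out after multiple imputation of missing HADS values at T0 and T2, so the 90% is the power claimed for the primary analysis. The same section later describes missing outcomes as arising from "dropouts (not filling the questionnaires at T0–T2, approx. 20% per group").

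**The concern.** A family without T2 data does not carry the same information as a family with it. A valid multiply imputed analysis adds the between-imputation variance to the ordinary sampling variance, and this is how the missing outcomes show up in the standard error. A power calculation that enters 330 and 230 as if all were observed leaves that term out.

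The article's own dropout assumption removes more than a third of the T2 outcomes, so the term is not small. If the primary comparison is not significant, readers will judge it against 90% power for a 12-point difference, and the planned analysis does not have that power.

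**Working it through.** **Inputs, all from Sample size unless noted**
- Responder rates 28% (intervention) and 16% (control); 5% level. Sidedness is not stated; two-sided reproduces the article's figures and one-sided does not.
- Planned families 330 and 230.
- Retention 0.8 × 0.8 = 0.64, so the loss is 1 − 0.64 = 36%. Observed at T2: 330 × 0.64 = 211.2 and 230 × 0.64 = 147.2, matching the article's 211 and 147, or 358 of 560 families.
- Primary analysis after multiple imputation of HADS (Statistical methods).

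**Step 1: reproduce the stated figures.** Exact Fisher power is the sum, over all pairs (x, y), of Bin(x; n1, p1) × Bin(y; n2, p2) for those pairs whose Fisher p-value is at most 0.05.
- 330/230, 28% vs 16%: 91.7% two-sided (continuity-corrected normal 90.5%, pooled normal 92.2%; one-sided Fisher 95.1%). This is the stated 90%.
- 211/147, 30% vs 16%: 86.0% (continuity-corrected 84.3%, pooled normal 87.3%). This is the stated 85%.

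Both figures are right for the inputs used. The 90% needs every one of the 560 families to be observed.

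**Step 2: same effect, families expected to have T2 data.**
- 211/147, 28% vs 16%: 74.8% (continuity-corrected 72.3%, pooled normal 76.5%).

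**Step 3: power after multiple imputation.** With M imputations, the pooled variance is T = W + (1 + 1/M) × B, where W is the mean within-imputation variance and B the between-imputation variance. Using 330/230, 36% missing, M = 20 and a pooled risk difference for 28% vs 16%:
- Binary response imputed within arm, no predictors: 77.7% (20,000 runs). This normal-theory test is slightly more liberal than Fisher's (it rejects 5.5% of the time when both rates are 20%), which accounts for part of the gap to 74.8%.
- Binary response imputed with T1 correlated 0, 0.5 or 0.7 with the T2 outcome: 76%, 79%, 80% (1,500 runs each).
- Continuous HADS imputed from T0 and T1 under a normal model, T0–T2 correlation 0.5–0.7 and T1–T2 correlation 0.6–0.8: 83–85% (1,500 runs, Monte Carlo error about 1 point).

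The article gives none of these correlations. They are assumptions.

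**Step 4: favourable limits.**
- If T1 fully predicted T2, or if total loss were only 20%, the effective sample would be 330 × 0.8 = 264 and 230 × 0.8 = 184: Fisher power 84%.
- If imputation recovered half of the lost information, the retained share would be 0.64 + 0.36 × 0.5 = 0.82, or 271/189: 85%.

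None of these reaches 90%.

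**The case against.** The best defence is that 75% is too pessimistic for what is planned. The article imputes HADS scores, not a yes/no response, and response is the change from T0 to T2. Baseline HADS is available for most dropouts and predicts that change. The endpoint also needs a response in only one parent, so a family with one observed responder is already classified even if the other parent is missing. The first part stands: the normal-model simulation gives 83–85%, so the complete-case 74.8% should not be printed as the power of the primary analysis. The second part could help further, but no calculation here has put a size on it. Neither is shown to bring the figure to 90%.

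A reader might go further in four ways that the document does not support:
- **That the loss is concealed.** The dropout, the 211 and 147, and a complete-case power all stand in the next sentence. The 30% used there is the article's own expected intervention-group rate. At 30% versus 16% the complete-case power is 86.0%, so the 85% is sound.
- **That the dropout figures contradict each other.** The 20% in Statistical methods can be read as a rate per interval, which agrees with "After exclusion of dropouts of 20% per group between T0 and T1 and again 20% between T1 and T2". It is ambiguous and not shown to be wrong.
- **That slow enrolment lowers power further.** Trial status reports that "On September 29, 2020, 406 families have been assigned, 216 into IG and 190 to CG", with an anticipated end date of 31 December 2020. It also says that enrolment ends when the target has been included. If it runs to 560, no further loss arises.
- **That there is an arithmetic slip or too few families.** Both stated powers reproduce, and the sample size was built from what the regions could recruit, not solved from the power.

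**Conclusion.** The claim that a 28% versus 16% difference is "identifiable at the 5% significance level with a power of 90"% in the imputed population does not hold under the article's own dropout assumption. The calculation is correct for 560 observed families; the premise that imputed families count in full is wrong. Complete-case power for that difference is about 75%, and the pooled imputed analysis lies at roughly 75–85%, a shortfall of about 5 to 15 points from the stated figure.

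This rests on 36% loss by T2, dropout completely at random in the simulations, a two-sided 5% test, and assumed correlations between HADS measurements. The upper end also assumes one normally distributed score per family, so it is illustrative. The lower end should not be read as the established power of the primary analysis, because where it falls in the range depends on an imputation model that the article does not specify and need not. The conclusion concerns the stated power only. It does not touch the endpoint, the test or the number of families.

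**What to change.** In Sample size:
- Replace the 90% with the power of the pooled, multiply imputed analysis for 28% versus 16%, computed under the 36% loss and a stated assumption about the imputation model. Expect a figure or range of about 75–85%.
- Report the complete-case power for the same effect (about 75% on 211 and 147) beside the existing 85% for 30% versus 16%, so that the two analyses can be compared at one effect size.

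In Statistical methods, say whether the approximate 20% dropout is per interval, so that it agrees with the 36% cumulative loss.

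The cost is text and one short simulation, with a less favourable published power. No extra families are needed, and the analysis does not change.

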## Statistical methods

Treatment groups will be described by their baseline variables. To investigate potential bias from non-randomization statistical tests corresponding to their distribution (Fisher’s test, *t* test, Wilcoxon test) will be performed to compare both groups. Baseline variables with significant differences will be considered as potential confounders in the following multiple regression analyses.

The primary analysis will be performed using the intention-to-treat principle being a conservative approach in superiority studies. Families enrolled in the CG in Bonn that claims great need for support will be analyzed as belonging to the CG. Only after the expiration of the study period, corresponding to approximately 12 months after inclusion (considering completion of T2 plus corresponding reminders), families may receive the intervention. The observation units will be the families, the parents, or the children. Cluster adjustment for families will be done, if appropriate. The primary analysis is the comparison of HADS response rates on the family level (MID ≥ 1.6 in at least one of the two parents) after 9 months between the IG and CG, using Fisher’s exact test. To adjust for potential confounders in this non-randomized trial, model-based secondary multiple regression analyses will be carried out for the following target variables on family level: HADS response in at least one parent, continuous HADS subscores for depression and anxiety separately for the healthy parent and parent with the disease, DT dichotomized for the cut-off point ≥ 5 for the healthy parent, PA-F-P-KF for the healthy partner, PCQ for the parent with the disease, FAD overall score and subscores for the family, and on children’s level KIDSCREEN for the children aged 8 and upwards. The sociodemographic and disease-specific variables will be included as confounders. Cluster adjustment according to the regions will take place using a corresponding random effect. Supplementary region-specific analyses will be carried out. Differences between the regions will be investigated using an extended interaction model with the independent variables of the region and interaction of the region with IG/CG. In the analysis of the KIDSCREEN questionnaire, the children (≥ 8 years old) will be the observation units, the adjustment will be made for the family cluster using additional random effects. The primary analyses will be carried out after the imputation of missing values of HADS at T0 and T2 by multiple imputations.

The subpopulation with statutory health insurance (SHI) data will be investigated separately. The distribution of baseline variables will be compared between the subpopulations with and without SHI data. The target variables based on the SHI data will be analyzed descriptively and compared between IG and CG on individual level clusters adjusting for families. Costs and uptake will be analyzed in the health economic evaluation. Missing values for the clinical outcomes may arise due to dropouts (not filling the questionnaires at T0–T2, approx. 20% per group) or incomplete details.

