## Methods/design

### Trial design

Through a pilot project in Aachen, this new form of care described here has already completed the phases of theory formation, modeling, and exploratory testing, including phase II in accordance with Campbell et al. [13] and feasibility testing or piloting in accordance with MRC (Medical Research Council) [14] under the name “Brückenschlag.” Within the follow-up project family-SCOUT, interventional levels described are now to be modeled in an appropriately complex evaluation design in order to test the benefits and appropriateness [15] and the degree of success of the intervention’s implementation. This study design combines elements of clinical effectiveness and implementation research in an effectiveness-implementation hybrid study type 2 [16]. The family-SCOUT effectiveness evaluation is based on a quasi-experimental, non-randomized control group design with two study arms (an intervention group (IG) and a control group (CG)), as well as one time point for preliminary measurement and two time points for follow-up measurements.

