### Primary and secondary outcomes

The intervention effectiveness will be examined using primary and secondary target variables collected at three measurement points, presented in the variables plan (Fig. 2; see the trial Standard Protocol Items: Recommendations for Interventional Trials (SPIRIT) Checklist for details (in Additional file 1)). The primary endpoint is a reduction in anxiety and depressive symptoms in at least one parent, assessed via the HADS response. HADS response is defined as an HADS reduction between T0 and T2 of at least the minimal important difference (MID) of 1.6.

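### Two unreconciled rules choose the confounders for the secondary models, and T0 HADS, named in neither, enters only if it passes a baseline significance screen

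*Protocol article*

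**What the plan says.** The Protocol article describes a "quasi-experimental, non-randomized control group design with two study arms" (Trial design). Under Statistical methods it gives two statements on covariates.

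- **Screen.** To look for bias, "statistical tests corresponding to their distribution (Fisher’s test, *t* test, Wilcoxon test) will be performed to compare both groups". Then: "Baseline variables with significant differences will be considered as potential confounders in the following multiple regression analyses". No significance level is given for these tests.
- **Fixed class.** In the paragraph on the regressions: "The sociodemographic and disease-specific variables will be included as confounders". No test condition is attached.

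The adjusted models are secondary: "To adjust for potential confounders in this non-randomized trial, model-based secondary multiple regression analyses will be carried out". The primary analysis is an unadjusted Fisher's exact test of family-level response, and response is a change score: "HADS response is defined as an HADS reduction between T0 and T2 of at least the minimal important difference (MID) of 1.6" (Primary and secondary outcomes). Neither statement names the T0 value of HADS, or of any other outcome, as a covariate.

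**The concern.** A variable confounds when it differs between the groups and also predicts the outcome. A baseline p-value ignores the second condition and mixes the first with sample size. A screen of this kind can leave out a strong predictor with a moderate imbalance and let in an irrelevant variable that differs by chance.

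T0 HADS is where this matters most. It is one of the two terms in the response definition. High scorers tend to move down towards the mean, and low scorers have little room to fall. It is not plainly a sociodemographic or a disease-specific variable, so the only stated route into the models is the screen. The adjusted models exist to deal with non-random allocation. If they omit an imbalanced T0 HADS, part of the baseline difference is read as a treatment effect.

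**Working it through.** **1. The plan's own power figures.** Sample size gives 330 and 230 families, 28% versus 16%, Fisher's exact test at 5%, power 90%; and 211 and 147 complete cases, 30% versus 16%, power 85%. Enumerating both binomials for the two-sided test gives 0.917 and 0.860. The dropout arithmetic also holds: 330 × 0.64 = 211 and 230 × 0.64 = 147. These figures are not in dispute. The planned difference is 28 − 16 = 12 points.

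**2. How often the screen flags a true imbalance.** Assumption: two-sided 5%, the only level in the article, and one T0 score per family. For a true standardised difference s,

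- SE = √(1/n₁ + 1/n₂), z = s/SE
- P(flagged) = P(Z > 1.96 − z) + P(Z < −1.96 − z)

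At 330 and 230, SE = √(1/330 + 1/230) = 0.0859, so an observed difference must reach 1.96 × 0.0859 = 0.17 SD to be flagged. At 211 and 147, SE = 0.1074 and the threshold is 0.21 SD. For s = 0.15 at full size, z = 0.15/0.0859 = 1.746 and P(flagged) = P(Z > 0.214) + P(Z < −3.706) = 0.415.

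| True imbalance | Unflagged, 330/230 | Unflagged, 211/147 |
|---|---|---|
| 0.10 SD | 79% | 85% |
| 0.15 SD | 58% | 71% |
| 0.20 SD | 36% | 54% |
| 0.30 SD | 6% | 20% |

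**3. What an unadjusted imbalance does to family response.** The article gives no HADS mean, SD or T0–T2 correlation, and does not say whether the 1.6 applies to a subscale or the total score. Both were simulated with no treatment effect, 400,000 families per run. Assumptions: integer scores; subscale 0–21 with mean 8 and SD 4, or total 0–42 with mean 15 and SD 7.5; two parents correlated 0.3 and both shifted at T0; both groups regressing to a common mean. A mean rise from T0 to T2 was used only to bring family response near the planned rates. Runs with family response between 15% and 38%:

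| Score | T0–T2 correlation | Mean rise | Family response | Shift for 0.15 SD |
|---|---|---|---|---|
| Subscale | 0.5 | 2 | 31.9% | 3.3 points |
| Subscale | 0.5 | 4 | 15.2% | 2.2 points |
| Subscale | 0.7 | 2 | 22.7% | 2.0 points |
| Subscale | 0.8 | 2 | 15.2% | 1.2 points |
| Total | 0.5 | 4 | 37.9% | 3.1 points |
| Total | 0.5 | 8 | 18.3% | 2.3 points |
| Total | 0.7 | 4 | 29.1% | 2.4 points |
| Total | 0.8 | 4 | 21.6% | 1.5 points |

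The shift is 1.2 to 3.3 points, or 1.2/12 = 10% to 3.3/12 = 28% of the planned difference. With no mean rise, family response is 44% to 62% and the shift 2.2 to 3.6 points. Runs with family response below 10% give 0.3 to 1.1 points.

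**4. How strongly T0 predicts response.** In the eight runs tabulated, a parent's chance of response is 1% to 7% in the lowest quarter of T0 scores and 16% to 44% in the highest. About 4% to 5% of parents start at 0 or 1, where a fall of 1.6 is impossible.

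**The case against.** The strongest reply is that the second statement already brings in sociodemographic and disease-specific variables whatever their p-value, and that the screen can be read as adding to that set. This stands: a reader who infers that confounders in general are chosen by significance testing goes further than the text. It does not help T0 HADS, which neither statement names. That it enters only through the screen is still an inference from silence, and an analysis plan that is not shown may settle it. What the article does fix is the screen, and that can be criticised as it stands.

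Other stronger readings also fail:

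- **That T0 HADS decides whether a response is possible.** It does so only at scores of 0 or 1. Elsewhere it changes how likely a response is.
- **That the primary result is affected.** "The primary analysis is the comparison of HADS response rates on the family level (MID ≥ 1.6 in at least one of the two parents") takes no covariates, so neither the screen nor its removal changes it.
- **That the confidence intervals are too narrow.** The screen uses covariates and group, not outcomes. The harm is residual bias, and no undercoverage of consequence was shown.
- **That adjustment is the only safeguard.** The article also plans region-specific analyses and a region-by-group interaction, and Bonn contributes families to both groups.

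It is also fair to say that the screen mostly misses small imbalances. At full size an observed difference above about 0.17 SD is flagged, so the shift quoted for 0.15 SD is near the most that the screen can leave in place.

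**Conclusion.** The concern holds in this limited form. The article states a significance screen beside an unconditional class of covariates, does not reconcile them, and names T0 HADS in neither. At 330 and 230 families, a true 0.15 SD imbalance would go unflagged about 58% of the time. Left unadjusted, it would move family response by roughly 1 to 3 points against a planned 12. That is not enough to produce the planned effect by itself, but it matters for models whose purpose is to remove such differences.

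The detection figures rest on an assumed two-sided 5% level. The bias figures rest on assumed HADS distributions and on regression to a common mean; a stable difference between the groups would give a smaller shift. The point concerns the secondary regressions only. It is a change that should be made, not one that undermines the trial.

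**What to change.** In Statistical methods:

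1. Delete the selection of confounders by baseline significance.
2. Keep the sociodemographic and disease-specific variables as a fixed set, and state that they enter whatever the baseline comparison shows.
3. Add the T0 value of the outcome as a fixed covariate in each secondary regression. For family-level HADS response, use the T0 HADS of each participating parent, with a stated coding for single-parent families.
4. Describe baseline balance by standardised differences in place of p-values.

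Recruitment phase should not be added to every model as a matter of routine: in Bonn the control group was recruited first and the intervention group second, so within that region phase and group cannot be separated.

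The cost is a change of wording and a few more model terms. T0 HADS is already needed for the endpoint. The planned rates imply about 330 × 0.28 + 230 × 0.16 = 92 + 37 = 129 responding families, which leaves room for those terms. The primary Fisher's exact test and the sample size stay as they are.

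### Fisher's exact test does not fit the planned multiple imputation, and the 90% power counts imputed families as if they had been observed

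*Protocol article*

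**What the plan says.** Statistical methods states: "The primary analysis is the comparison of HADS response rates on the family level", to be made "after 9 months between the IG and CG, using Fisher’s exact test". The same paragraph ends: "The primary analyses will be carried out after the imputation of missing values of HADS at T0 and T2 by multiple imputations". The article gives no rule for combining the results from the imputed data sets.

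Sample size sets the groups at "IG = 265 + 65 = 330; CG = 70 + 160 = 230" and states that "a difference of 28% (IG) versus 16% (CG) will then be identifiable at the 5% significance level with a power of 90" per cent. The numbers behind this are given as "after imputation for missing values for dropouts, 330 in the IG, 230 in the CG". The same section assumes "dropouts of 20% per group between T0 and T1 and again 20% between T1 and T2", which leaves 211 and 147 families. For these it claims 85% power for a complete-case comparison of 30% with 16%. The last paragraph of Statistical methods, before the health-economic part, puts dropout over T0 to T2 at about 20% per group.

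**The concern.** Multiple imputation gives valid inference by averaging an estimate over the completed data sets and adding the between-imputation variance to its standard error. Fisher's test supplies neither an estimate nor a standard error, only a conditional p-value per completed table. The two prescribed elements therefore do not fit together as written, and every valid way of joining them replaces or transforms the named test.

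Two things are at stake. The first is the error rate of the single confirmatory test, if completed tables were analysed as though observed. The second is the power claim. The Sample size section credits the imputed analysis with more power (90%) for a smaller difference (12 points) than the complete-case analysis has (85%) for a larger one (14 points). Imputation cannot deliver that unless auxiliary data recover the lost information.

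**Working it through.** **Inputs.** From Sample size: 330 and 230 families; 28% versus 16% with 90% power; 211 and 147 completers; 30% versus 16% with 85% power. Missing by T2 is 1 − 0.8 × 0.8 = 36% (Sample size) or about 20% (Statistical methods, read as cumulative). Assumptions of this check: two-sided 5% level, outcomes missing completely at random, 20 imputations.

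**1. The plan's own figures.** Exact power of two-sided Fisher's test, by enumerating both binomials:
- 330/230, 28% v 16%: 91.7% (stated 90%).
- 211/147, 30% v 16%: 86.0% (stated 85%).

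Both are reproduced. The 90% is thus the power for 560 fully observed families.

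**2. The same difference without the dropouts.** With little auxiliary information, valid imputation carries about as much information as the completers. Fisher's test for 28% v 16% has 74.8% power with 211/147 (36% missing) and 84.4% with 264/184 (20% missing; 330 × 0.8 and 230 × 0.8).

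Normal approximation for 211/147:
- pooled rate = (211 × 0.28 + 147 × 0.16)/358 = 0.2307
- null SE = √[0.2307 × 0.7693 × (1/211 + 1/147)] = 0.0453
- alternative SE = √[0.28 × 0.72/211 + 0.16 × 0.84/147] = 0.0432
- z = (0.12 − 1.96 × 0.0453)/0.0432 ≈ 0.72, so power is about 77%.

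**3. Type I error if completed tables are treated as observed.** Let f be the observed fraction, with imputation within arm and no auxiliary data.
- Averaging over many imputations, the true variance of the rate is 1/f times what the test assumes. The error is 2[1 − Φ(1.96√f)]: 8.0% at f = 0.80 and 11.7% at f = 0.64.
- One completed set has variance factor 1/f + (1 − f)²/f + (1 − f): 1.50 at f = 0.80 and 2.125 at f = 0.64. The error is 2[1 − Φ(1.96/√factor)]: 11.0% and 17.9%.

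Fisher's test is somewhat conservative, so simulated rates lie slightly lower (response 16-30%, 20,000 to 40,000 trials per setting):

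| Rule | 20% missing | 36% missing |
|---|---|---|
| Fisher, one completed set | about 10% | about 17% |
| Fisher, median p of 20 sets | about 7.4% | about 11% |
| Fisher p as signed z, pooled by Rubin's rules | about 4.5% | about 4.5% |
| Risk difference, Rubin's rules | about 5% | about 5% |

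**4. Power with valid pooling, 28% v 16%.** At 36% missing: 77% (risk difference; 78% in a second simulation) or 75% (pooled z). At 20% missing: 86% or 84%. These agree with step 2.

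**5. Sensitivity to the imputation model, 36% missing.** A continuous score was imputed with an auxiliary predictor of correlation 0, 0.5 or 0.7 (1,500 trials each). One completed set then rejects in about 13%, 11% and 8% of null trials, and the median p in about 9%, 7% and 6%. If the arm is left out of the imputation model there is no inflation (4-5% for one set, 1-3% for the median p), but that model pulls the arms together and dilutes a real effect.

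**The case against.** The strongest objection is that a combining rule, the number of imputations and the imputation model are details a condensed article may leave to the full protocol or analysis plan, neither of which is shown. That is right: the missing rule alone is no finding. What remains is the pairing of a named test with a named missing-data method that it does not fit, and a published power figure that no later detail makes correct for the stated dropout.

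A reader might infer three stronger things that the article does not support:

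- **That the plan has a type I error of 12-17%.** Those rates need Fisher's test on a single completed set or a median p-value, the higher dropout figure, imputation within arm and weak auxiliary information. The text names neither rule, and because it calls for multiple imputation, using a single set would depart from it. The use of 330/230 in a power calculation is not an instruction for the analysis.
- **That Fisher p-values cannot be pooled, so the test cannot be carried out.** They can be converted to signed z scores and pooled by Rubin's rules, which held the error at about 4.5%. The result is no longer an exact test, and the route has to be specified.
- **That 36% missing is settled.** Statistical methods gives about 20%, at which the inflation and the power loss are both smaller. The two figures agree only if the 20% is meant per interval, which the text does not say.

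The imputation is also of HADS scores, not of the binary family response, so observed scores may recover some information. That softens both the inflation and the power loss by an amount the article does not let one calculate.

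**Conclusion.** The point holds in a limited form. Fisher's exact test is a poor match for multiple imputation, because Rubin's rules do not apply to it directly, and the Sample size section counts imputed families as full information.

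Treating completed tables as observed would give a type I error of about 7-10% at 20% missing and 11-17% at 36% missing. This assumes imputation within arm with little auxiliary information; strong predictors lower it. With valid pooling the error is about 5%, and the 90% power for 28% versus 16% becomes about 75-78% at 36% missing or 84-86% at 20% missing, unless auxiliary data recover information. The power shortfall is the firmer part, since it follows from figures the article states; the inflation depends on a combining rule that it does not state. All these figures rest on data missing completely at random, and the simulated ones on 20 imputations.

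**What to change.** - Make the primary test the unadjusted risk difference or log odds ratio for family-level HADS response, pooled over imputations by Rubin's rules and referred to the corresponding t distribution.
- Keep Fisher's exact test for the complete-case analysis.
- Reconcile the two dropout figures, and restate the power for the missing information expected under the reconciled figure. Any gain credited to auxiliary data should be stated as an assumption.
- Leave the adjusted regression of the same endpoint as the secondary analysis already planned.

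The change takes a few sentences and no new data. Its cost is that the stated power becomes less favourable and the primary test is no longer exact.
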